### *GSteps* development

*GSteps* is a self-directed web-based interactive Game designed to increase stepparenting, co-parenting and marital skills for adults in stepfamilies. The initial phase of *GSteps* development involved an extensive literature review regarding healthy stepfamily functioning and satisfying stepcouple relationships (Santos et al., 2018; Santos et al., 2020). Factors unique to stepfamilies (e.g., stepparent-stepchild relationships) as well as factors that are common to all couples (e.g., communication skills) were used to build the *GSteps* intervention components. A total of 15 components were considered and incorporated into three content areas/modules: *Conjugality* – *Module 1* (emotional divorce, financial issues, positive communication skills, enhance the social support network, remarriage unrealistic beliefs, stress management strategies and conflict management strategies). *Stepparenting – Module 2* (positive stepparent-stepchild relationships, development of relationships within stepfamily, stepparenting roles definition, stepfamily’ unrealistic beliefs, loyalty binds related to stepparents and develop share meaning); *Co-parenting – Module 3* (positive co-parenting strategies and loyalty binds related to co-parents). The entire structure and contents of *GSteps* were demonstrated in Figure 3.

**Figure 3 fig3:**
[figure not shown]
Branching scenario of the entire structure of *Gsteps.*

After determining the content of each topic and module, the developers dramatized fictional but real-life based narratives in a theater script to tell the story of a stepfamily that includes a mother (Teresa), an eight-year-old daughter (Maria), and a stepfather (António). These three characters were voluntarily represented by three actors from *Teatro Amador de Sandim* and gave us your written consent to record and release your image. Prior to dramatization, a spoken reflection was made separately including four volunteer target users: two interviewees (a stepmother and a stepfather) lived in a simple stepfamily (only one adult bring children from past relationships) and other two (a mother and a stepfather) lived in a complex stepfamily (both adults bring children from past relationships). We will collect feedback from subjects in different conditions (simple and complex) because the roles that they assume within the stepfamily are also different. In other words, in complex stepfamilies, both members of couple are simultaneously a parent (from their own children) and a stepparent (from partner’ children); but in simple stepfamilies the men and the women never have these two roles simultaneously.

Based on pilot feedback from the two major types of stepfamilies, changes in characters’ speeches, facial and body expressions were made to clarify the meaning of the content and dramatization. Before watching the videos, participants access the Game’s objectives and learn about the technical features. After that, the three actors present themselves as members of the stepfamily and their previous families’ history (e.g., stepfather is divorced and does not have kids). This information helps the participant to know the context of the presented family’s life cycle.

Each module lasts between 10 and 20 min. Each is presented in a sequential video dramatization with some or all family members portraying relationship challenges (components). Videos freeze to ask participants which would be the better option in the face of a given conflict. Participants are able to see how their chosen option could play out. There are *right*, *wrong*, and *not the best* options, and a message pops up with a psychoeducational content focusing on positive and successful practices of stepparenting, co-parenting and remarital functioning to guide the participant to the right answer. All videos have subtitles to facilitate participants’ comprehension. For example, in module 2, the participant will see an argument between Maria and her stepfather on what Maria said – *You are not my father! Do not order me!* Then, the video freezes and a question pops up – *What would be Antonio’s best answer?* The participant will have three options – (1) *Punish Maria*; (2) *Ask Maria’s mother for help*; (3) *Explain to Maria what is his role within the stepfamily* and (4) *Watch the video again*. If the participant chooses option one (wrong option), he/she will see a video with António punishing Maria and Maria denying him authority. Then, the video freezes and a psychoeducational massage will appear – *initially, discipline and authority must be imposed by the biological parent; Maria and António have not yet developed a trust relationship, because of that, she has difficulties in recognizing his authority*. Option two is the “not the best option.” If selected, another psychoeducational massage arises – *While it is very important for the biological parents to support the decision of the stepparents, it is even more important for the stepparents to clearly assume their role within the family. How could António assertively tell Maria what is his role in the family?* Only option three is correct and if participant choose it, he/she will see the correct video with the correct behavior and the Game goes forward (see the sequence of images in Figure 4). Participants are encouraged to finish all modules and have the opportunity to communicate with a mental health professional for clarification of doubts or emotional support, if desired. The Game platform is checked daily to monitor participation. Participation reminders are sent weekly to finish the *GSteps* in the allotted time – 1 month.

**Figure 4 fig4:**
[figure not shown]
Branching scenario from Scene 10 of Module 2-“Stepparenting.”

*Wait-list*. After replying to the baseline questionnaire (*T_0_*), participants assigned to this condition receive a message informing that they are on the waiting list to participate on the course. The wait-list CG is also notified that they will be receiving further instructions in 1 month, and that access to the course is be possible after replying to a second assessment (*T_1_*).

## Data and statistical proposed analysis

Data will be analyzed using the Statistical Package for Social Sciences (SPSS), v.24 (IBM Corp, 2016). Preliminary and descriptive statistics will be conducted to describe the sociodemographic characteristics of the participants, standard deviations (SDs) and data normality. Missing data will be manage through intention-to-treat analysis (ITT). The Chi-square (*χ*^2^) and the independent sample *t*-test will be used to detect significant differences between the EG and CG on the *T_0_* sociodemographic characteristics and psychosocial variables. To explore the effect of the intervention on psychosocial variables and intervention perceived benefits, researchers will conduct repeated measures mixed ANOVAs to analyze the interaction between groups (EG and CG) and time (baseline, post-test and follow-up for EG; baseline and post-test for CG). To analyze the main effects, *post hoc* tests using Bonferroni correction will be performed. The independent *t* test will be used to compare how satisfied the EG and the CG are with the psychoeducational simulation Game on the post-intervention assessment (*T_1_*).

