### Power analysis

G*Power (Faul et al., 2007) was used to calculate a minimum sample size. To test the efficacy of the intervention compared with the control condition, we propose a power analysis based on a probability level of 0.05 and a power of 0.80 (Hawkins et al., 2008; Lucier-Greer and Adler-Baeder, 2012). For analysis of covariance (ANCOVA), G*Power indicated an entire sample of 74 to detect a medium effect size of *d* = 0.5. However, a high dropout rate (about 50%; Wangberg et al., 2008) is usually encountered in internet-based interventions and thus we ultimately plan for a sample of 112 participants (56 participants per condition).

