## Strengths and limitations

Several strengths of the protocol and its design must be highlighted. This is a program that focuses on adults in stepfamilies, a vulnerable and understudied group, namely in the Portuguese context. This protocol underlines the importance of adapting psychoeducational intervention programs to the current demands of everyday life, namely, the exponential use of technological and virtual resources. Furthermore, literature suggest that online interactive multimedia programs can offer effective delivery of general education content (Cairncross and Mannion, 2001; Gelatt et al., 2010). As with other web-based interventions, this approach has a brief format, is low-cost and has a broad reach. The existence of subtitles in all videos enhances this reach and makes it possible to adapt the *GSteps* to other languages. Furthermore, it is a very comfortable type of intervention in which participants can receive the intervention from computer-devices in their own homes.

Moreover, by performing repeated measurements of psychosocial variables related with marital domain (dyadic marital adjustment; marital social skills; remarriage beliefs), parenting domain (SAB and CAB) and family functioning through a longitudinal and RCT design, this research protocol facilitates more reliable data on the outcome effects of the intervention. There are also some limitations of the protocol. All included measurement instruments are self-reports that can lead to a response-set tendency. Nonetheless, the majority of instruments are standardized inventories with good levels of reliability and validity or instruments that are tailor-made for the protocol. An expected limitation is the dropout rate during the intervention process as well as a significant missing data to follow-up assessment. To minimize this limitation, participants should be regularly notified by email to continue/end the *GSteps* or to participate in the post-and follow-up assessments.

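### Intention-to-treat is named as the missing-data method, but the ANOVA named beside it needs every participant's T1 score; unless values are imputed, the efficacy analysis is completers-only under an ITT label

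*Protocol article*

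**What the plan says.** All references are to the protocol article.

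- **Data and statistical proposed analysis**, on missing data: "Missing data will be manage through intention-to-treat analysis (ITT"). No imputation or likelihood method is named anywhere in the article.
- **Same section**, on efficacy: "researchers will conduct repeated measures mixed ANOVAs to analyze the interaction between groups (EG and CG) and time". The time levels are "baseline, post-test and follow-up for EG; baseline and post-test for CG". On software: "Data will be analyzed using the Statistical Package for Social Sciences (SPSS), v.24".
- **Power analysis**: "However, a high dropout rate (about 50" per cent) is said to be usual in internet-based interventions. On that ground a required sample of 74 is raised to 112, or 56 per arm.
- **Strengths and limitations**: "An expected limitation is the dropout rate during the intervention process as well as a significant missing data to follow-up assessment". The countermeasure is regular e-mail, covering both the Game and the later assessments.
- **GSteps development, wait-list paragraph**: for the control group (CG), access to the course "is be possible after replying to a second assessment" (T1). The experimental group (EG) has the Game from allocation.
- **Recruitment and randomization**: allocation follows completion of T0, so a participant lost before T1 has baseline data only.

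**The concern.** The article does not simply leave the missing-data method for later. It states one, and what it states defines an analysis set. A classical repeated measures ANOVA needs a value at every time level for each participant, and the standard SPSS procedure for it deletes incomplete cases. The two statements therefore pull apart: one promises that everyone randomised is analysed, and the other removes everyone without T1. If follow-up were entered as a third level, all of CG would be removed, because CG has no T2.

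Two features make this more than a matter of wording. The article itself plans for heavy loss. The reasons to answer T1 also differ by arm: CG members must answer to get the Game, while EG members already have it, and whether they answer may depend on how they got on with it. A completer comparison is biased when response is related to outcome differently in the two arms. The report would then claim a protection that the analysis did not give.

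**Working it through.** **1. The plan's own figures.** The article gives 74 evaluable, about 50% dropout and 112 randomised.
- 74 × 1.5 = 111, which becomes 112 when rounded up to an even number.
- Division by the retained fraction gives 74 / (1 − 0.5) = 148.
- Retaining 74 of 112 allows for 1 − 74/112 = 34% loss.

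The inflation is a separate matter. It is shown here because it fixes how many completers remain.

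**2. Participants a complete-case analysis would use.** If 50% lack T1 in each arm, 112 × 0.5 = 56 remain, about 28 per arm, against the required 74.

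**3. Power at 56.** Inputs from Power analysis: d = 0.5 and "a probability level of 0.05 and a power of 0.80" (two-sided taken; sidedness is not stated). For two equal groups f = d/2 = 0.25. ANCOVA power comes from a noncentral F with noncentrality N·f²/(1 − ρ²), where ρ is the baseline–outcome correlation. The article does not give ρ.

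| ρ (assumed) | N for 80% power | Power at N = 56 |
|---|---|---|
| 0 | 128 | 45% |
| 0.65 | 75 | 68% |
| 0.66 | 73 | 69% |

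The stated 74 is reached only at ρ of about 0.65 to 0.66, so 0.65 is used below.

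**4. Size of bias in the test actually named.** With two time points, the group × time test equals a comparison of mean change. This was simulated for completers only, under these assumptions:
- 56 per arm, no true effect, ρ = 0.65 and unit SD at T0 and T1, so the SD of change is √(2 × (1 − 0.65)) = 0.84;
- 50% missing in each arm, with CG missing at random;
- log-odds of EG response rising with the participant's own change, by the slope shown per SD of change.

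| Slope | Mean EG − CG difference in change (outcome SD) | False positives at 5% |
|---|---|---|
| 0 | 0.00 | 5.6% |
| 0.5 | 0.20 | 15% |
| 1.0 | 0.35 | 36% |

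Relative to d = 0.5, the last two are 0.20/0.5 = 40% and 0.35/0.5 = 70%. With 20% missing in CG instead of 50%, the differences are almost the same (0.20 and 0.34), with false positives of 16% and 41%. In this illustration, what matters is the link between response and change in EG; the overall amount missing in CG matters little.

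**The case against.** The strongest defence is that this is a condensed article. Read in good faith, the sentence commits to keeping everyone randomised and leaves the technique to an analysis plan that is not shown. The unequal time levels listed for the two arms could even suggest that a likelihood mixed model was meant. This stands in part: completers-only is an inference, and an unstated imputation or mixed model would change it. It does not rescue the sentence, which names ITT as the method and pairs it with an ANOVA.

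A reader might also infer more than the documents support:

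- **That half of the T1 data will be missing.** The 50% is a cited typical dropout rate for internet interventions, used for planning. It is not stated as T1 non-response. Strengths and limitations separates dropout from the intervention from missing follow-up, and someone who leaves the Game can still answer T1.
- **That EG loses half while CG is nearly complete, and that this is the planned 50%.** That pattern is about 25% missing overall, leaving roughly 84 of 112, which is above 74.
- **That the bias can equal the effect sought.** The largest illustrated value is 0.35 SD, against 0.5.
- **That a shift in the raw T1 mean measures the bias.** With half retained, that shift is 0.798 times the correlation between response and T1, so 0.24 SD at 0.3. The named test is on change. If response relates to T1 only through T0, T0 shifts by 0.798 × 0.3/0.65 = 0.37, and change by 0.24 − 0.37 = −0.13, which is smaller and opposite in sign.
- **That ANOVA is the only efficacy model mentioned.** Power analysis names ANCOVA. It too loses participants without T1.
- **That EG is bound to respond less.** EG receives weekly reminders, and e-mails about the later assessments are planned. The CG incentive is real, but the direction and size of differential loss are unknown.

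**Conclusion.** The point holds in limited form. ITT is offered as a missing-data method and is not one, and the ANOVA named with it excludes participants without T1. Unless an unstated imputation is used, the analysis covers completers only while carrying the ITT label, in a trial that plans for about 50% dropout and gives only CG a condition for answering T1.

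The consequence cannot be sized from the article. It is nil if missingness is unrelated to change. It is about 0.20 to 0.35 SD in the change comparison if EG response depends on own change as assumed above (50% missing per arm, correlation 0.65, no true effect). Those slopes and the correlation are illustrative assumptions, not forecasts. The conflict between the two statements rests on none of them.

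**What to change.** Replace the missing-data sentence and the T0–T1 part of the ANOVA sentence so that the plan states the following:

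1. All randomised participants are analysed in the arm to which they were allocated.
2. The T0–T1 contrast is estimated by a likelihood-based linear mixed model on all available T0 and T1 data. ANCOVA with multiple imputation by arm is an alternative. With perhaps 28 observed outcomes per arm, the imputation should use a small set of predictors. Both are available in SPSS.
3. The EG-only T2 data are kept out of this contrast.
4. The primary analysis assumes data are missing at random.
5. T1 response is reported by arm.
6. One missing-not-at-random (delta) sensitivity analysis is added. This is needed because response that depends on own change, as in the illustration, is not missing at random, and neither method in item 2 can be relied on to remove that bias.
7. T1 is requested from every EG participant, whether or not the Game was finished. The planned e-mails partly cover this; the plan should say it outright.

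The cost is a few lines of text and slightly more analysis work. Intervals may be wider. Little power is recovered, because a participant with T0 only adds almost nothing to the T1 difference. The wording should be settled before outcome data are seen, so that the choice of method is not data-driven.

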## Procedure

### Recruitment and randomization

*GSteps* can be called an intervention, psychoeducational activity, or “Game.” Recruitment will be announced in social media (i.e., Facebook, Instagram, Self-help forums) or through a project website. On all these platforms, a link to an online questionnaire (*T_0_* – pre-test assessment) should be available. Participants meeting inclusion criteria and consenting to enter the study proceed and complete the pre-test questionnaire. After that, an automatic equation set will randomly (1:1) allocate participants to the EG or to the CG. Based on the random assignment, an automatic message is sent. Participants in the EG are invited to play *GSteps* and receive an email with a link and a confidential username and password. Participants allocated in CG receive an email informing them that they are on the waiting list. Both participants and the research team will be blind to the assignment.

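### The sample size is computed for ANCOVA, but the planned efficacy test is a group-by-time mixed ANOVA, which needs 2/(1+r) times as many participants for the same power

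*Protocol article*

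**What the plan says.** The Power analysis section of the protocol article sets its targets as follows: "we propose a power analysis based on a probability level of 0.05 and a power of 0.80". It then names the test and the result: "For analysis of covariance (ANCOVA), G*Power indicated an entire sample of 74 to detect a medium effect size of" d = 0.5. To allow for a dropout of about 50%, it concludes: "thus we ultimately plan for a sample of 112 participants (56 participants per condition").

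The section Data and statistical proposed analysis names a different test for efficacy: "researchers will conduct repeated measures mixed ANOVAs to analyze the interaction between groups (EG and CG) and time". The time factor differs by arm: "baseline, post-test and follow-up for EG; baseline and post-test for CG". Study design and Instruments and measures agree that T2 is for the experimental group, because the wait-list arm gets the game once T1 is complete. ANCOVA is not mentioned in the analysis section. That section does plan chi-square and t-tests of T0 differences between arms, but it describes no adjustment for T0 scores.

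**The concern.** The article states both the test that was powered and the test that will be run, and they differ. This is therefore a contradiction within the text and not a detail left to a fuller document.

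The two tests do not have the same precision. A mixed-ANOVA interaction on two time points carries the full noise of both measurements into the difference. ANCOVA removes only the part of T1 that T0 predicts. If the trial is run as written, the 80% power does not belong to the reported test, and precision is given away although the T0 score needed to recover it is already collected. ANCOVA would also absorb chance baseline imbalance, which the plan only tests for.

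**Working it through.** **Inputs from the article.** Alpha 0.05 (taken as two-sided, since sidedness is not stated), power 0.80, d = 0.5, 1:1 allocation, 74 before dropout, 112 planned, dropout about 50%.

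**Assumed input.** The correlation r between T0 and T1 scores is not given, so it is varied from 0.3 to 0.8. SDs are taken as equal across arms and time points.

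**Step 1: reproduce 74.** For two equal groups, Cohen's f = d/2 = 0.25, so f² = 0.0625. Noncentral-F power with numerator df 1, two groups, one covariate and noncentrality N × 0.0625 (no variance explained by the covariate) gives a total of 128, not 74. Putting r in through N × 0.0625/(1 − r²), 74 gives 80% power at r = 0.653. The figure 74 also comes out if 0.5 is entered as f with numerator df 10. The article does not say how it was obtained.

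**Step 2: what the interaction tests.** The control group has T0 and T1 only, so the group-by-time contrast between arms uses those two points. With two time points, its F is the square of the t statistic comparing mean T1 − T0 change between arms.

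**Step 3: residual variances, in units of the outcome variance.**
- Change score: 1 + 1 − 2r = 2(1 − r).
- ANCOVA of T1 on arm and T0: 1 − r² = (1 − r)(1 + r).
- Ratio: 2(1 − r)/[(1 − r)(1 + r)] = 2/(1 + r), which exceeds 1 for every r below 1.

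**Step 4: numbers at d = 0.5, two-sided 0.05.** Noncentrality is N × 0.0625 divided by the residual variance. For N = 74 the numerator is 4.625. At r = 0.5 that gives 4.625/0.75 = 6.17 for ANCOVA and 4.625/1.00 = 4.63 for the interaction.

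In each paired column, ANCOVA comes first and the interaction second.

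| r | 1 − r² | 2(1 − r) | 2/(1 + r) | Completers for 80% | Power, 74 analysed | Power, 56 analysed |
|---|---|---|---|---|---|---|
| 0.3 | 0.91 | 1.40 | 1.54 | 118 / 178 | 60.4% / 43.4% | 48.6% / 34.2% |
| 0.5 | 0.75 | 1.00 | 1.33 | 98 / 128 | 68.8% / 56.4% | 56.4% / 45.1% |
| 0.65 | 0.5775 | 0.70 | 1.21 | 76 / 90 | 79.7% / 71.8% | 67.6% / 59.3% |
| 0.7 | 0.51 | 0.60 | 1.18 | 68 / 78 | 84.4% / 78.2% | 73.0% / 66.0% |
| 0.8 | 0.36 | 0.40 | 1.11 | 48 / 54 | 94.2% / 91.8% | 86.5% / 82.8% |

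The completer totals are rounded up to even numbers, so their ratios differ slightly from 2/(1 + r).

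**Step 5: at the r that makes 74 right.** With r = 0.653 the interaction needs 90 completers, and 90/74 = 1.22 (the formula gives 1.21). With 74 completers it has 72% power.

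**Step 6: after the stated dropout.** 112 × (1 − 0.5) = 56, which is the last column of the table.

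**The case against.** Under randomisation the T0–T1 interaction is a valid, unbiased test of the treatment effect. ANCOVA buys efficiency and does not correct a bias. The contradiction could also be settled by keeping the interaction and re-sizing for it. Both points stand, which is why this is a matter of alignment and lost power and not of a wrong answer. At high r the loss is small: about 94% against 92% at r = 0.8 with 74 analysed.

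It might be said that 112 leaves slack. If all 112 were analysed, the interaction would have 74.6% power at r = 0.5 and 88.0% at r = 0.65. But the article assigns the step from 74 to 112 to dropout, and at its own rate only 56 complete.

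Three stronger readings are tempting, and the document does not support them.
- A reader might infer a fixed penalty such as 18–33%. That range is r = 0.7 to 0.5, and the article gives no r.
- A reader might take 74 as a sound ANCOVA figure and inflate it, to 74 × 1.18 = 87 or 74 × 1.33 = 98. Step 1 shows that 74 does not follow from the stated inputs alone. If r is 0.5, even 98 falls short of the 128 that the interaction needs.
- A reader might infer that moving to ANCOVA restores 80% power. With 56 completers it does so only at the high end of the range of r.

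**Conclusion.** The mismatch is certain: both tests are named in the article and they are not the same. The direction is also certain given equal SDs, since the planned test needs more participants than the powered one for any r below 1. Its size depends on r, which has to be assumed: an excess of 54% at r = 0.3, 33% at 0.5, 21% at 0.65, 18% at 0.7 and 11% at 0.8. With 74 analysed, the loss is about 12 percentage points of power at r = 0.5 (68.8% to 56.4%) and 8 at r = 0.65 (79.7% to 71.8%).

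The plan should be changed, because the gain needs no further data. Whether 80% power was ever secured for ANCOVA, and whether 112 covers 50% dropout, are separate weaknesses of the sample-size section. They limit what this correction can achieve.

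**What to change.** 1. In Data and statistical proposed analysis, make the efficacy analysis of each primary and secondary outcome an ANCOVA of the T1 score on arm, with the T0 score of the same scale as covariate. Report the adjusted mean difference with its 95% CI.
2. Use the T2 data, which exist only in the experimental group, for within-arm description of stability. Keep the mixed ANOVA as a secondary analysis at most.
3. In Power analysis, state the r assumed and how 74 was obtained, and restate the power for the test actually used at the number expected to complete. If the interaction is kept as the efficacy test, size for it instead: about 128 completers at r = 0.5, or 90 at r = 0.65.

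Items 1 and 2 cost only wording, since T0 is already collected on these scales and SPSS, the package named, fits the model. Item 3 may show that more participants are needed. At 50% dropout, ANCOVA would need 98/0.5 = 196 recruited at r = 0.5, or 76/0.5 = 152 at r = 0.65.

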### Aims

To fill the gaps in the literature, our protocol intends to evaluate the efficacy and feasibility of a new web-based psychoeducational intervention (*GSteps*). The protocol outlines a comparison with a non-intervention control condition in a sample of Portuguese speaking adults in stepfamilies (parents and stepparents). The protocol offers options to examine changes in *stepparenting and co-parenting attitudes, remarriage beliefs, dyadic marital adjustment, marital social skills* and *family function.*

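### The named follow-up tests are attached to the ANOVA main effects, not to the group-by-time interaction that carries the intervention effect

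*Protocol article*

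**What the plan says.** Under 'Data and statistical proposed analysis', the stated purpose is "To explore the effect of the intervention on psychosocial variables and intervention perceived benefits". The method is "repeated measures mixed ANOVAs to analyze the interaction between groups (EG and CG) and time", with the time levels given as "baseline, post-test and follow-up for EG; baseline and post-test for CG". The next sentence opens "To analyze the main effects" and reads in full "To analyze the main effects, *post hoc* tests using Bonferroni correction will be performed". No follow-up of the interaction is named for the psychosocial outcomes. The one direct comparison of the arms at T1 concerns satisfaction: "The independent *t* test will be used to compare how satisfied the EG and the CG are".

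Three other sections bear on this:

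- 'Aims' frames the trial as a controlled comparison: "The protocol outlines a comparison with a non-intervention control condition".
- 'Instruments and measures' rests efficacy on T0 and T1 and reserves T2, in the EG only, for stability of change.
- 'Power analysis' sizes the trial on an ANCOVA. The analysis section does not list that method.

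**The concern.** A group-by-time interaction is the right place to look for the effect of GSteps. Once it has been tested, the reader needs the between-arm contrast behind it. The article sends the follow-up tests to the main effects instead.

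- **Group.** This term averages T0, completed before randomisation, with T1. The expected difference at T0 is zero, so the term shows half the T1 effect.
- **Time.** This term pools both arms. Retesting, regression to the mean or season would move it as readily as GSteps would.
- **Redundancy.** With two arms and two shared visits, a pairwise test of either main effect repeats its own F test. Only comparisons with T2 add anything, and they have no concurrent control.

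At stake is what accompanies the interaction test in the report. It would be either a diluted group comparison or a change over time that randomisation does not protect.

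**Working it through.** **The plan's own figure.** The article's only sizing figure is 74 for an ANCOVA with d = 0.5, alpha 0.05 and power 0.80. With f = d/2 = 0.25, two groups, one covariate and a two-sided test, I get 128; power at 74 is 0.56. A total of 75 results if an unstated baseline correlation of about 0.65 is built in: f = 0.25/sqrt(1 − 0.65²) = 0.329. So 74 does not follow from the stated inputs. That is a separate matter, and nothing below depends on it.

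**Inputs from the article.** N = 112 (56 per arm), 1:1 allocation, d = 0.5, alpha 0.05 (taken as two-sided), and shared visits T0 and T1.

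**Assumptions, not in the article.** SD 1 at both visits; T0-T1 correlation r of 0.4, 0.5 or 0.7; all 112 analysed; where drift is considered, a change of 0.2 or 0.3 SD common to both arms.

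**A true T1 effect of 0.5 SD.** Each standardised effect is multiplied by sqrt(56/2) = 5.292 to give the noncentrality of a t test (110 df; 109 for ANCOVA). At r = 0.5:

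- Group main effect: (0 + 0.5)/2 = 0.25. The SD of the two-visit mean is sqrt((1 + r)/2) = 0.866. Standardised 0.289, noncentrality 1.528, power 0.328.
- Interaction on T0/T1: 0.5/sqrt(2(1 − r)) = 0.500, noncentrality 2.646, power 0.746.
- ANCOVA, T1 given T0: 0.5/sqrt(1 − r²) = 0.577, noncentrality 3.055, power 0.857.

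| r | Group main effect | Interaction | ANCOVA |
|---|---|---|---|
| 0.4 | 0.35 | 0.67 | 0.82 |
| 0.5 | 0.33 | 0.75 | 0.86 |
| 0.7 | 0.30 | 0.92 | 0.96 |

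A simulation of 10,000 trials per scenario agrees at r = 0.5: 0.325 for group and 0.745 for the interaction.

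**No effect of GSteps, with a common drift.** The noncentrality of the time main effect is drift/sqrt(2(1 − r)) × sqrt(112). At r = 0.5 this is 0.2 × 10.583 = 2.117 and 0.3 × 10.583 = 3.175, so the term is significant with probability 0.555 and 0.882. At r = 0.7 the simulation gives 0.77 and 0.98.

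**Error rate of the tests between arms.** In the same null simulations, over all drifts and with 56 or 28 per arm, the interaction rejected in 4.7% to 5.3% of trials and the group main effect in 4.4% to 5.4%. Only the time term responds to drift.

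**If half are lost.** The power section cites about 50% dropout, which leaves 28 per arm. The multiplier becomes sqrt(28/2) = 3.742. At r = 0.5, power is 0.19 for group (noncentrality 1.080), 0.45 for the interaction (1.871) and 0.56 for ANCOVA (2.160). The ordering is unchanged.

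**The case against.** The strongest reply is that the efficacy test is already right. The sentence before the post hoc one ties the intervention effect to the interaction. On T0 and T1 that interaction is exactly the EG-CG difference in change, and under randomisation its expectation is the T1 difference. This stands. A reader might infer that the plan never estimates the difference between the arms; the article does not support that.

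A reader might also infer that the plan will declare effects when GSteps does nothing. That is not supported either. The interaction and the group term hold about 5%. A significant time term under drift correctly detects a change that both arms share, and no section says it will be counted as efficacy. Misreading it is a risk, not a stated intention.

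The phrase may be loose wording for simple main effects after an interaction, or may mean pairwise comparisons over the three EG visits. The text does not settle which. The second reading is not redundant, and it fits the use of T2 for stability. But any comparison with T2 is within the EG, with no control, so it cannot follow up the between-arm question.

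Finally, this is a condensed article. Effect sizes, confidence intervals and exact contrasts may sit in a document not shown, so their absence carries no weight here. What remains is a follow-up rule that the article does state, and it points to the wrong terms.

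**Conclusion.** The point holds in a limited form. The planned test of GSteps is sound. The only follow-up tests named are tied to terms that do not measure its effect. The group term carries half the effect, with power of 0.30 to 0.35 where the interaction has 0.67 to 0.92. The time term can be significant with no intervention effect, in 56% or 88% of trials for a shared drift of 0.2 or 0.3 SD at r = 0.5. The correlations and drifts are assumptions, and these figures take all 112 as analysed. They show why main effects should not serve as follow-up to the efficacy test; they do not measure a loss in the planned interaction test.

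There is also a gain to be had. The T1 difference adjusted for T0 targets the same effect as the interaction under randomisation but is a different and more powerful test: 0.82, 0.86 and 0.96 against 0.67, 0.75 and 0.92 at r = 0.4, 0.5 and 0.7. It also avoids the empty control cell at T2.

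**What to change.** Replace the post hoc sentence with: *The intervention effect is the EG minus CG difference at T1 adjusted for T0 (ANCOVA, as in the power analysis), with the T0-T1 group-by-time contrast as a supporting analysis. Main effects of group and time are not taken as evidence of efficacy. EG change to T2 is descriptive.*

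The power section names ANCOVA but not its covariate, so it should add that the covariate is the T0 score. The cost is a sentence of analysis wording. T0 and T1 are already collected in both arms, and no more participants are needed. The only loss is the main-effect comparisons.
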